#### Primary Objective Analyses

The primary objective of this study is to identify the most efficient intervention package that is expected to produce the greatest benefit to survivors’ sexual health with the fewest (and least-intensive) intervention components. This objective will be achieved using an “all-active components” optimization criterion to guide a decision-making process with systematic data analysis [39]. The main and interaction effects of components will be computed using a generalized linear model (GLM) approach to ANOVA with effect coding to compare the average change in sexual morbidity aggregated across experimental conditions [66].

A model will be conducted for effects on sexual distress, measured by the FSDS-DAO; this model will be prioritized for the intervention optimization decision-making process. First, only components (and component levels) that have a beneficial independent effect (ie, a small-to-moderate positive main effect [Cohen *d≥*0.3]) on sexual distress will be provisionally included. Next, these provisional decisions will be reviewed by examining component interaction effects. Components will be considered for addition to the intervention package if they have important (ie, Cohen *d≥*0.3) synergistic effects, meaning they amplify the benefit of another component in the package. Components will be considered for removal from the package if they have important (ie, Cohen *d≥*0.3) antagonistic effects, meaning they reduce the benefit of another component in the package. Decisions will be informed by computing parsimonious prediction models for outcomes from both the main and interaction effects of the included components [39].

A subsequent model will be conducted for sexual functioning among women reporting sexual activity within the past 4 weeks, measured by the FSFI. Model results will be compared between sexual distress (full population) and sexual functioning (sexually active population only). Components (and component levels) provisionally included based on the sexual distress model findings may be removed if there is a substantial negative effect on sexual function. While discrepant or antagonistic results between the sexual distress and sexual functioning models are possible, they are unlikely, given that FSDS-DAO and FSFI total scores have been found to be highly correlated (*r=*–0.65 [49]).

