#### Sample Size and Power Analysis

This factorial trial has been powered to detect a small-to-medium effect size (ie, Cohen *d*=0.30) of intervention components on sexual morbidity outcomes. This represents the smallest effect size that the study team determines would offset the required resources of an intervention component to be delivered to and completed by participants in an optimized intervention. Determined using the MOST R package [60] *FactorialPowerPlan* function (R version 3.6.2; R Foundation for Statistical Computing), 247 survivors of breast cancer would be needed to detect Cohen *d*=0.30 of change in sexual distress from baseline to 24-week assessment (measured by FSDS-DAO) at 80% power with α=.05 for all main effects and interaction effects of the intervention components. In a factorial experimental design with only 2 levels per factor, the power to detect main effects and interaction effects is equal [39,61]. This power analysis assumes a pretest-posttest correlation in sexual distress of *r*=0.65, which is supported by data from the investigators’ prior research (Female Sexual Distress Scale pretest-posttest *r*=0.73; N=28) [32] and by Female Sexual Distress Scale validation data (pretest-posttest *r*=0.62; N=318) [49]. The effect size of Cohen *d*=0.30 is reasonable to expect from intervention components, given that prior randomized controlled trials of interventions containing the components demonstrated large effects on sexual distress relative to control (Cohen *d*=0.87 and Cohen *d*=0.59) [28,32]. Conservatively accounting for an estimated 20% attrition (based on the investigators’ past trials) [32,42,62] and rounding up to achieve a balanced number of participants per condition, 320 survivors will be randomized in the trial (247/0.80=309 rounded to a total N=320, for n=20 per each of the 16 factorial conditions).

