### Data Analysis Plan

#### Overview

In accordance with the NIH requirement, a Data Safety and Monitoring Plan has been established to guide study oversight and ensure the safety of participants and data validity and integrity. Summaries of primary and secondary measures will be reviewed for completeness every 6 months by the WF NCORP RB Data Safety Monitoring Board, along with other key study metrics such as recruitment, retention, patient characteristics, and adverse events. More details about trial oversight and monitoring are available in Multimedia Appendices 3 and 4.

Study methods have been designed to avoid missing data, including efforts to retain participants with incentives and assessment reminder protocols, as well as requiring responses to all items on web-based assessment questionnaires. As it is not possible to entirely avoid missing data, restricted maximum likelihood estimation will be used to address missing data in analyses under a missing at random (MAR) assumption [63-65]. Proposed analyses are robust against MAR data [63,64]. The National Academy of Sciences guidelines for missing data will be followed [64], and the impact of missing data on study conclusions will be explored with sensitivity analyses. Specifically, attrition rates across study conditions will be compared. If a particular condition has a markedly higher dropout rate, baseline covariates that predict attrition will be identified in secondary analyses. Variables determined to predict loss to follow-up will be included in sensitivity analysis models to satisfy the conditions described by Little and Rubin [65] for data to be considered MAR.

Primary analyses will be intention to treat, meaning that the randomized condition assignment will be included in models regardless of whether the participant completes their assigned Cores or not. Sensitivity analyses will examine the effects by whether assigned Cores are completed or not. All participants with at least 1 follow-up assessment will be included in analyses. All tests of hypotheses and reported P values will be 2 sided.

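### The primary model analyses FSDS-DAO change with no baseline covariate; the sample size is right for that choice, but adjusting for baseline would cut the variance by 17.5% at the planned correlation at no cost

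*Protocol article*

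**What the plan says.** Under Primary Objective Analyses, main and interaction effects are to be computed with a generalized linear model "approach to ANOVA with effect coding to compare the average change in sexual morbidity aggregated across experimental conditions". Table 1 and Sexual Morbidity Outcomes both define the primary evaluation as FSDS-DAO change from baseline to 24 weeks. No baseline covariate is named. The Overview of the Data Analysis Plan brings in covariates only for attrition, in sensitivity models.

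The sizing follows the same line. Under Sample Size and Power Analysis, "247 survivors of breast cancer would be needed to detect Cohen *d*=0.30 of change in sexual distress from baseline to 24-week assessment", "at 80% power with α=.05 for all main effects and interaction effects of the intervention components". The text adds: "This power analysis assumes a pretest-posttest correlation in sexual distress of *r*=0.65". Two sources are cited in support: the investigators' earlier work ("Female Sexual Distress Scale pretest-posttest *r*=0.73; N=28") and scale validation data with r=0.62 and N=318. Allowing for 20% attrition and rounding to equal cells gives 320 randomized.

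Under Procedures, the baseline assessment is completed before randomization.

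**The concern.** Subtracting baseline fixes its coefficient at 1. With a correlation well short of 1, that over-corrects and leaves variance that a fitted baseline coefficient would remove. Under randomization both analyses target the same component effect, and in large samples the adjusted one is never less precise.

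Two things depend on this. One is the power claimed for every main effect and interaction. Under a change-score analysis that power leans heavily on the assumed correlation, and the planned 0.65 lies above the estimate from the larger of the two sources. The other is the selection decision: components enter or leave the package according to whether an estimated d reaches 0.3, so the standard error of that estimate governs how often a component is misclassified.

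**Working it through.** **Inputs.** d=0.30, 80% power, α=0.05 and r=0.65 come from Sample Size and Power Analysis. The test is two-sided ("All tests of hypotheses and reported P values will be 2 sided", Data Analysis Plan, Overview). The cited correlations are 0.62 (N=318) and 0.73 (N=28). Expected completers are 320×0.80=256.

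**Set-up.** In a 2⁴ factorial with effect coding, every effect contrasts N/2 women with N/2. With residual variance v in units of the raw-score variance, SE=√(4v/N) and the noncentrality is d/SE, here on N−16 degrees of freedom. Assuming equal variances at baseline and 24 weeks:
- change score: v=2(1−r)
- baseline-adjusted: v=1−r²
- 24-week score alone: v=1

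**The plan's own figure, r=0.65.**
- change score: v=2×0.35=0.70, N=247, as stated
- baseline-adjusted: v=1−0.4225=0.5775, N=204
- no use of baseline: v=1, N=351

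Of these three, only the change score gives 247, and it does so whether the model has 2, 5, 11 or 16 parameters. Then 247/0.80=308.75, which rounds up to 309 and then to 320 for equal cells. The match also shows that the plan's d is scaled to the raw-score SD.

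**Variance ratio.** (1−r²)/[2(1−r)]=(1+r)/2. At r=0.65 this is 0.825, a saving of 17.5%. In sample-size terms, 256/0.825≈310, or about 54 more completers' worth of information.

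**Power for d=0.30 with 256 completers.**

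| r | v, change | v, adjusted | Power, change | Power, adjusted | N for 80%, change | N for 80%, adjusted |
|---|---|---|---|---|---|---|
| 0.62 | 0.760 | 0.6156 | 78.3% | 86.1% | 268 | 217 |
| 0.65 | 0.700 | 0.5775 | 81.5% | 88.2% | 247 | 204 |
| 0.73 | 0.540 | 0.4671 | 90.2% | 93.8% | 191 | 166 |

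At r=0.62 the change-score analysis would need 268/0.80=335 randomized. With 256 completers, its power drops below 80% once r is under about 0.636.

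**Effect on selection, r=0.65, N=256.** The SE of the estimated d is √(4×0.70/256)=0.105 for change and √(4×0.5775/256)=0.095 adjusted. For a true d of 0.2 or 0.4, the chance that the estimate lands on the wrong side of 0.3 is, by the normal approximation, about 17% (z=0.1/0.105) against about 15% (z=0.1/0.095).

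**The case against.** The strongest reply is that the plan is valid and coherent. The outcome definition, the analysis and the sizing all concern change, and 247 is correct for it. The planned 0.65 lies between the two cited values and inside the 95% interval around r=0.62 with N=318 (Fisher transformation, about 0.55 to 0.68). All of this stands. A reader might infer that the sample size is wrong or the trial underpowered; the document does not support either. The shortfall is 1.7 points (80% less 78.3%) and occurs only at the smaller cited correlation. At the larger one, unadjusted power is 90.2%.

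A second reply is that the article merely does not mention covariates, that a model of change may still include baseline, and that the full protocol or analysis plan could add it. This stands in part: the unseen documents may do so, and the article's use of restricted maximum likelihood with all women who have at least one follow-up leaves the final model less settled than a plain change score. But the article does state a model, and its sample size matches the unadjusted version of that model and not the adjusted one. It is therefore fair to comment on the choice as published.

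Third, chance imbalance across 16 cells of 20 is a tempting extra argument, but it should not be used. Effects are aggregated over about 160 against 160 randomized, so imbalance in single cells is not what drives them.

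Fourth, components are selected on an estimated d≥0.3 and not on significance. A component with a true d of exactly 0.30 clears the threshold about half the time under either analysis, so the rise in power is not a rise in correct selection. That is right. For selection, the benefit is the smaller standard error, and it is modest.

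**Conclusion.** The point holds as a loss of efficiency and not as an error. At r=0.65 the published primary model carries a variance 1/0.825, or about 1.21, times that of a baseline-adjusted model. With 256 completers, adjustment adds 6.7 points of power at r=0.65, 7.8 at r=0.62 and 3.6 at r=0.73, and keeps power above 80% at every correlation the protocol cites. For selection, it lowers the standard error of d from about 0.105 to 0.095.

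The figures assume equal variances at baseline and 24 weeks, d scaled to the raw-score SD (the reading that reproduces 247), and 20% attrition. If the full protocol or analysis plan already adjusts for baseline, confirming that settles the matter.

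**What to change.** Add mean-centred baseline FSDS-DAO as a covariate to the effect-coded primary model, and baseline FSFI to the FSFI model. Within the planned restricted maximum likelihood framework, model the 12- and 24-week scores with baseline-by-visit and component-by-visit terms and take the 24-week contrast as primary. This also gives women who have only a 12-week score a defined place in the model.

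State that the d compared with the 0.3 threshold is the adjusted effect divided by the raw-score SD, not by the smaller residual SD. Otherwise adjustment would itself inflate d and shift the selection rule.

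Keep 320 randomized, and report expected power as about 88% at r=0.65 and 86% at r=0.62. The cost is a sentence or two in the plan, with no new data or participants. It should be settled before any outcome data are seen by condition.

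### The 80% power describes a significance test, but components are chosen by an estimated d of at least 0.3, which a component at the target effect of 0.30 passes about half the time

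*Protocol article*

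**What the plan says.** Under Sample Size and Power Analysis, the protocol article states: "This factorial trial has been powered to detect a small-to-medium effect size (ie, Cohen *d*=0.30) of intervention components on sexual morbidity outcomes". On the meaning of 0.30 it adds: "This represents the smallest effect size that the study team determines would offset the required resources of an intervention component". The resulting number is given as "247 survivors of breast cancer would be needed to detect Cohen *d*=0.30 of change in sexual distress from baseline to 24-week assessment", "at 80% power with α=.05 for all main effects and interaction effects of the intervention components". The calculation assumes a pretest-posttest correlation of 0.65. Dividing by 0.80 for attrition gives 309, rounded to 320 randomized. The Overview of the Data Analysis Plan adds: "All tests of hypotheses and reported P values will be 2 sided".

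The decision rule is in Primary Objective Analyses. Its first step keeps only components with "a small-to-moderate positive main effect [Cohen *d≥*0.3]) on sexual distress will be provisionally included". The second step reviews interactions with the same cut-off: "Components will be considered for addition to the intervention package if they have important (ie, Cohen *d≥*0.3) synergistic effects". A matching sentence covers removal for antagonistic effects. None of these steps carries a P value or a confidence limit. The only P<.05 criterion in the analysis plan is in the Moderation section.

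**The concern.** Sample size and decision rule both use 0.30, but for different things. In the power calculation 0.30 is the assumed true effect, and a component counts as detected when its test is significant. In the decision rule 0.30 is the bar that the effect must clear. The true effect is never observed, so the bar is applied to the estimate. An estimate centred on 0.30 falls below 0.30 about half the time, whatever the sample size.

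The optimized package is the trial's primary product, and the Limitations section says that a follow-on randomized trial will test it. A reader who sees 80% power at the smallest worthwhile effect may take it as the chance that a component of that size enters the package. The rule as written does not give that chance. The article also does not say by which SD the rule's d is divided, and the answer depends on it.

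**Working it through.** **Inputs.** From Sample Size and Power Analysis: d=0.30, power 80%, α=.05, r=0.65, evaluable N=247, attrition 20%, N randomized 320. From the Overview of the Data Analysis Plan: two-sided tests. From Trial Design: 16 conditions from four two-level factors; with 20 per condition, each main effect compares half of N with half of N. Expected completers: 320 × 0.80 = 256. Assumption: equal SD at baseline and at 24 weeks.

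**Step 1: reproduce the plan's figure.** In units of the raw-score SD, the SD of change is √(2(1−0.65)) = √0.70 = 0.837.
- Normal approximation: N = 4 × (1.960+0.842)² × 0.70 / 0.30² ≈ 244.2, or 123 per half, so 246.
- Noncentral t: 247, with power 80.1%. This matches.
- 247/0.80 = 308.75, rounded up to 309. This matches.
- Other scales do not match: ignoring the correlation gives 350 to 351, and an ANCOVA residual SD of √(1−0.65²) = 0.760 gives 202 to 204.

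The sample-size calculation is therefore sound, and its d is in raw-score SD units.

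**Step 2: precision of the estimated d.** SE(d) = 2 × 0.837/√N.
- N=247: 0.106
- N=256: 0.105
- N=320: 0.094

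**Step 3: chance of passing the d≥0.3 step.** P = 1 − Φ((0.30 − true d)/SE). At true d=0.30 this is 1 − Φ(0) = 50% at any N. The true d needed for 80% is 0.30 + 0.842 × SE: 0.39 at N=247 or 256, and 0.38 at N=320.

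**Step 4: compare with the powered test.** At N=256 the smallest significant estimate is 1.97 × 0.1046 = 0.206. The 0.3 cut-off is stricter, so requiring significance as well changes nothing. A simulation of the full 2⁴ model (N=256, true d=0.30, 20,000 runs) gave an estimate of at least 0.3 in 50.0% of runs, P<.05 in 81.4%, and both in 50.0%.

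Chance of inclusion at the first step, N=256, raw-score SD units:

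| True d | Estimate ≥0.3 | Beneficial, two-sided P<.05 |
|---|---|---|
| 0 | 0.2% | 2.5% |
| 0.15 | 8% | about 30% |
| 0.20 | 17% | about 48% |
| 0.30 | 50% | about 81% |
| 0.39 | 80% | (0.39−0.206)/0.1046 = 1.76, so about 96% |
| 0.45 | 92% | (0.45−0.206)/0.1046 = 2.33, so about 99% |

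**Step 5: sensitivity to the scale of d in the rule.** Suppose the rule divides by the SD of change. A raw-scale 0.30 becomes 0.30/0.837 = 0.359 and the SE at N=256 is 2/√256 = 0.125, so P = Φ(0.059/0.125) = Φ(0.47) ≈ 68% (70% at N=320). Dividing by an ANCOVA residual SD gives about 77% to 80%, but the article describes an ANOVA on average change. If 0.30 is the target on the rule's own scale, the answer is 50% on any scale.

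**The case against.** The strongest defence is that the article makes no false statement. It claims 80% power to detect, and that is right for the test it describes. A reader might infer a stated 20% rate of losing worthwhile components, but the document gives no such rate. This part of the defence stands.

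The 50% also applies only at the break-even effect. A component at exactly 0.30 just repays its burden, so losing it costs little, and a true d of 0.45 is kept about 92% of the time. A cut-off at the smallest worthwhile effect suits the aim of a package with few components. This stands too: it would be wrong to conclude that worthwhile components in general are lost half the time.

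A reader might go further and divide the earlier package effects (d=0.59 and 0.87) among four components, concluding that the rule could select nothing from a package that works. The document does not support this. It says only that "prior randomized controlled trials of interventions containing the components demonstrated large effects on sexual distress relative to control". It does not say that those packages held exactly these four components or that effects add, and here the education factor compares enhanced with standard content. Components below 0.30 are in any case ones that the rule is meant to leave out.

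Finally, inclusion is provisional, interactions and prediction models inform the final decision, and the exact standardizer may be in a statistical analysis plan that is not shown. This softens the point without removing it. The stated route back into the package is a synergistic interaction of at least 0.3, so a component with only a main effect has none. The sexual-function model is described only as a reason for removal.

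**Conclusion.** The point holds as a mismatch between the sample-size justification and the decision rule. The stated 80% is not a property of the rule that produces the trial's primary answer. On the scale of the power calculation, a component at the smallest worthwhile effect passes the first step about 50% of the time, and 80% is reached only at a true d of about 0.39. If the rule's d is in change-score SD units, the figure at a raw-scale 0.30 is about 68%.

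These results assume r=0.65, equal SDs at the two times, about 256 completers, and a cut-off applied to the estimate. The last is an inference, but no other reading is workable without a test in the rule. The 50% covers the provisional main-effect step, not the final package. The sample size of 247 and the effect-size cut-off are each defensible. This should be fixed, but it does not invalidate the design.

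**What to change.** In Sample Size and Power Analysis, state that the 80% refers to the two-sided .05 test, and add the selection probability of the d≥0.3 rule: about 50% at a true d of 0.30 and 80% at about 0.39. In Primary Objective Analyses, define d on the scale of the power calculation, as the difference between component levels in mean change divided by the pooled baseline SD. Both changes are wording, need no data or participants, and should be made before outcomes are seen. The cost is a less favourable figure in print.

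As an option only, the investigators could base provisional inclusion on the powered test (a beneficial effect with two-sided P<.05, that is, an estimated d of about 0.21 or more). The chance of inclusion at 0.30 then rises to about 81%, but more components below the threshold are admitted: about 30% rather than 8% at a true d of 0.15, about 48% rather than 17% at 0.20, and 2.5% rather than 0.2% for an inert component. That trade-off is for the investigators to settle.

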#### Secondary Objective Analyses

Mediation and moderation will be examined separately and will follow the recommendations of prior work [66].

#### Mediation

An established strategy using structural equation modeling for testing mediation in a factorial experiment will be followed [67]. The mediation effects of components on both sexual distress and sexual functioning will be evaluated within a single model. Mediation hypotheses will be supported if (1) changes in the mediators influence the change in sexual morbidity, (2) intervention components influence the change in the mediators, and (3) changes in the mediators account for the relation between intervention components and changes in sexual morbidity.

In an optimization trial design, mediation analyses are critical both when components produce a positive effect and when there are null findings [68]*.* If there are null findings of components on primary outcomes, mediation analyses support the next research steps by determining where a breakdown may have occurred. For instance, a hypothesized mediator may influence the outcome, but the component did not adequately influence the mediator. This result would suggest that intervention revisions would be needed to better target the mediator. Mediator analyses are also critical to refining the study’s conceptual model.

